### Data collection and management

Data will be collected using standardized case report forms by trained research personnel. Each participant will be assigned a unique study identification number to ensure confidentiality. Data will be entered into a secure, password-protected electronic database by two independent data entry staff members (double data entry). Discrepancies will be resolved by referring to the original records. The database will be backed up regularly on encrypted institutional servers, and access will be restricted to authorized personnel.

### Adverse events and safety monitoring

All adverse events will be recorded throughout the study, with details on onset, duration, severity and their relationship to the intervention. Serious adverse events will be reported promptly to the ethics committee in accordance with institutional requirements. Participants experiencing significant adverse events may discontinue the study at the discretion of the investigator.

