Physical examination/safety check	×		×				
Interventions							
LLLT group		3 sessions	3 sessions				
Manual acupuncture group		3 sessions	3 sessions				
Outcome assessments							
ISI	×		×				×
PSQI	×		×				
FSS	×		×				
PHQ-9	×		×				
GAD-7	×		×				
HRV	×		×				
Process and safety monitoring							
Sleep diary	×	×	×	×	×	×	×
Adverse event monitoring		×	×	×	×	×	×
Concomitant medication recording	×	×	×	×	×	×	×
Dropouts/withdrawals		×	×	×	×	×	×
Participant adherence		×	×				

× indicates that the item is performed or assessed at the corresponding time point. LLLT, low-level laser therapy; ISI, Insomnia Severity Index; PSQI, Pittsburgh Sleep Quality Index; FSS, Fatigue Severity Scale; PHQ-9, Patient Health Questionnaire-9; GAD-7, Generalized Anxiety Disorder-7; HRV, heart rate variability. Week 0 indicates baseline, week 2 marks the end of treatment, and week 6 represents follow-up. Both interventions are delivered three times per week for 2 weeks, with six sessions in total. ISI is assessed at baseline, week 2, and week 6; PSQI, FSS, PHQ-9, GAD-7, and HRV are assessed at baseline and week 2. Sleep diaries, adverse events, concomitant medications, dropouts/withdrawals, and adherence are monitored as indicated.

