### Outcomes

#### Primary outcome

The primary outcome is the change in Insomnia Severity Index (ISI) total score from baseline to the end of the two-week intervention (week 2). The ISI is a 7-item self-report scale that assesses the severity of nocturnal and daytime components of insomnia over the past two weeks, with total scores ranging from 0 to 28. Higher scores indicate more severe insomnia. The ISI has been validated in Chinese populations and demonstrates good reliability and sensitivity to change (20, 21).

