#### Safety outcomes

Adverse events related to LLLT or acupuncture, such as skin irritation, transient dizziness, bleeding, hematoma or pain, will be monitored at each visit and recorded in standardized forms. Severity, duration and causal relationship with the intervention will be assessed and documented.

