### Participant timeline

Study procedures will take place at baseline (week 0), during the treatment phase, at the end of treatment (week 2), and at follow-up (week 6). Baseline assessments include demographic data, medical history, physical examination, ISI, PSQI, FSS, PHQ-9, GAD-7, and HRV. At week 2, ISI, PSQI, FSS, PHQ-9, GAD-7, and HRV will be reassessed, and a brief physical examination or safety check will also be repeated to support adverse-event monitoring. At week 6, only ISI will be reassessed to evaluate the persistence of the primary insomnia-severity outcome. Sleep diaries, adverse events, and concomitant medications will be monitored throughout the study as specified in **Table 3**.

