### Statistical analysis

All analyses will be performed using SPSS (version 26.0) or equivalent software. Two-tailed p-values < 0.05 will be considered statistically significant. The primary analysis will strictly follow the intention-to-treat (ITT) principle. For the primary superiority outcome, analysis of covariance (ANCOVA) will be employed. Although the primary endpoint is defined as the change in ISI from baseline to week 2, ANCOVA will be performed with the week-2 ISI score serving as the dependent variable, the treatment allocation (LLLT vs. acupuncture) as the fixed factor, and the baseline ISI score as a covariate (31). This approach is statistically equivalent to comparing change scores while providing better precision. Furthermore, this adjustment for baseline ISI is specifically chosen to align with the stratified block randomization procedure, thereby maximizing statistical power and precision in estimating the treatment effect.

Between-group differences in adjusted mean changes and their 95% confidence intervals (CIs) will be reported. Statistical superiority of LLLT over manual acupuncture for the primary endpoint will be considered supported if the two-sided p-value for the between-group difference is less than 0.05 and the entire 95% CI of the difference excludes zero in favor of the LLLT group (32).

The longitudinal trajectory of ISI across post-randomization assessments will be analyzed as a supportive repeated-measures analysis using a linear mixed-effects model. The model will include treatment group, time, and the group × time interaction as fixed effects, baseline ISI as a covariate, and participant-specific random intercepts to account for within-subject correlations. This model will be used to evaluate whether the between-group difference in insomnia severity is maintained at week 6.

Secondary continuous outcomes assessed at week 2 only, including PSQI, FSS, PHQ-9, GAD-7, and HRV indices, will be analyzed using analysis of covariance, with the week-2 value as the dependent variable, treatment group as the fixed factor, and the corresponding baseline value as a covariate. When model assumptions are markedly violated, appropriate transformations or non-parametric methods will be considered. A per-protocol analysis including participants with adequate adherence, defined as attending at least four of six sessions and having no major protocol deviations, will be performed as a sensitivity analysis.

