For the primary ANCOVA analysis, missing week-2 ISI data will be handled using multiple imputation under the missing-at-random assumption. The imputation model will include baseline characteristics, treatment allocation, and available outcome data, and results from imputed datasets will be combined using Rubin’s rules (33). For the supportive longitudinal ISI analysis, the linear mixed-effects model will use all available ISI observations under the same missing-at-random assumption. For secondary outcomes assessed at week 2 only, missing data will be handled using multiple imputation if the extent of missingness is substantial, and complete-case or imputation-based sensitivity analyses will be conducted as appropriate.

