### Ethics and dissemination

The study protocol has been reviewed and approved by the Ethics Committee of Guangdong Provincial Hospital of Traditional Chinese Medicine (Approval No. YF2025-141-01). The trial will be conducted in accordance with the Declaration of Helsinki and relevant national regulations. Written informed consent will be obtained from all participants prior to enrolment. Participants may withdraw from the study at any time without prejudice to their routine care (34).

The results of this trial will be disseminated through publication in peer-reviewed journals and presentations at national and international conferences, regardless of whether the findings are positive, negative or inconclusive. De-identified data may be made available upon reasonable request after publication, subject to ethical approval and data-sharing agreements.

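### The adverse-event rule allows exit from the study and does not separate stopping the intervention from stopping ISI assessment

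*Protocol article*

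**What the plan says.** The section on adverse events and safety monitoring states: "Participants experiencing significant adverse events may discontinue the study at the discretion of the investigator". The only other exit in the article, under Ethics and dissemination, is also from the study as a whole: "Participants may withdraw from the study at any time without prejudice to their routine care".

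The Statistical analysis section states: "The primary analysis will strictly follow the intention-to-treat (ITT) principle". For gaps in the primary outcome, "missing week-2 ISI data will be handled using multiple imputation under the missing-at-random assumption". The imputation model uses baseline characteristics, allocation and whatever outcome data are available.

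The ISI is taken at weeks 0, 2 and 6 only. The Participant timeline adds: "At week 6, only ISI will be reassessed to evaluate the persistence of the primary insomnia-severity outcome". The other questionnaires and HRV are repeated once, at week 2.

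Two places bear on participants who receive less than full treatment. The Table 3 footnote says: "Sleep diaries, adverse events, concomitant medications, dropouts/withdrawals, and adherence are monitored as indicated", with adherence and dropouts on separate rows. The per-protocol set requires attendance at four or more of the six sessions.

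**The concern.** An adverse event is a reason to stop needles or laser. It is seldom a reason to stop a short self-report form. An intention-to-treat analysis relies on outcomes being collected whatever treatment was received, and a rule that names the study as the thing to leave fits badly with that.

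Someone who leaves before week 2 has no post-baseline ISI. Imputation then predicts the week-2 value essentially from baseline and arm, and cannot reflect the event that led to the exit. If leavers do worse than predicted, their own arm looks too good. At stake are some week-2 and week-6 ISI values that could still have been obtained, and a possible small shift in the primary estimate.

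**Working it through.** **Plan figures used for scale.** The sample size section gives a difference of 2.5 ISI points, SDs of 4.44 (LLLT) and 3.9 (acupuncture), two-sided alpha 0.05 and 80% power. A Welch t-test gives 79.2% power with 44 per arm and 80.1% with 45, so 45 per arm reproduces. For 15% dropout, 45 / 0.85 = 52.9, so 53 per arm also reproduces. Nothing in that calculation is at fault here. The article does not say how much of the 15% would be adverse-event exits.

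**Shift formula.** Let f be the fraction of an arm whose week-2 ISI is lost through an adverse-event exit, and d the number of ISI points by which these participants are worse than their imputed values. With 1 = LLLT and 0 = acupuncture:

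shift towards LLLT = f1 × d1 − f0 × d0

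**Inputs.** The documents give neither f nor d. I assume f from 0 to 5% and d up to 4 points. Five percent of 53 is 2.65, or two to three people.

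| Assumed case | Shift towards LLLT (ISI points) |
|---|---|
| No adverse-event exits | 0 |
| LLLT only, 3%, d = 2 | 0.03 × 2 = +0.06 |
| LLLT only, 5%, d = 4 | 0.05 × 4 = +0.20 |
| Acupuncture only, 3%, d = 2 | −0.06 |
| Acupuncture only, 5%, d = 4 | −0.20 |
| 5% in each arm, d = 4 in LLLT and 2 in acupuncture | 0.20 − 0.10 = +0.10 |
| 5% in each arm, d = 4 in both | 0 |

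A simulation that replaced leavers' week-2 values by the completers' regression prediction gave +0.200, −0.202, +0.098 and −0.001 for the four cases with 5% leaving. This confirms the algebra but is no evidence for the inputs.

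**Against the planned effect.** 0.20 / 2.5 = 8%.

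**Against the precision of the estimate.** With baseline correlation r (not given, so assumed), the approximate ANCOVA standard error at 53 per arm is

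SE = sqrt[(4.44² + 3.9²) / 53 × (1 − r²)] = sqrt[0.659 × (1 − r²)]

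This is 0.774, 0.703 and 0.580 for r = 0.3, 0.5 and 0.7. The largest shift, 0.20, is then 26%, 28% and 34% of a standard error.

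**If only week 6 can still be collected.** A week-6 ISI can inform the imputation of week 2. With a week-2/week-6 residual correlation c and a share k of the departure persisting to week 6, the shift left over is f × d × (1 − c × k). Starting from 0.20:

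- c = 0.7, k = 1: 0.20 × 0.30 = 0.06
- c = 0.5, k = 0.5: 0.20 × 0.75 = 0.15

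Both c and k are assumptions. Late recovery helps only in part.

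**The case against.** The strongest reply is that this is an article condensing a fuller protocol and operating procedures that are not shown, and that follow-up after stopping treatment is commonly set out there. The sentence is also permissive: it obliges no one to leave and forbids no assessment. Adherence and dropout are tracked separately, and an attendance threshold for the per-protocol set only makes sense if some under-treated participants stay in the intention-to-treat set. Missing week-2 values have a stated method, and with recruitment complete little may be left to recover.

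Most of this stands and keeps the point minor. It does not remove it. The article does not merely stay silent on adverse-event exits. It states a rule, and that rule is to leave the study. No place in the article extends the retention implied by the per-protocol definition to someone who stops because of an adverse event.

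A reader might infer from the examples under Safety outcomes ("such as skin irritation, transient dizziness, bleeding, hematoma or pain") that acupuncture would lose more participants. The documents do not support that. The same list includes skin irritation and dizziness, and the LLLT group section monitors laser recipients for both, as well as for discomfort and visual discomfort. Either arm could lose more, or neither.

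**Conclusion.** The point holds as a minor wording problem with a cheap remedy. The rule allows avoidable loss of ISI values but does not itself cause it. Under the assumed inputs (0 to 5% leaving in one arm, up to 4 points worse than imputed) the shift in the primary estimate runs from zero to about 0.20 ISI points in either direction, at most 8% of the planned 2.5. The true size cannot be computed, because the documents give no adverse-event exit rate.

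Two stronger readings are tempting and not supported. One is that the rule contradicts the intention-to-treat analysis or bars follow-up. It does neither, since it is discretionary and the analysis states how missing values are handled. The other is that the trial is biased towards a particular arm. Nothing in the documents fixes the direction, or shows that leavers would have worse insomnia than predicted.

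**What to change.** Reword the adverse-event sentence along these lines: *A participant with a significant adverse event may stop the intervention if the investigator so decides. Unless the participant withdraws consent to data collection, every ISI assessment still due will be requested.*

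Report adverse-event discontinuations by arm, using the dropout and adverse-event data already recorded. Do not enter a late ISI as a week-2 value, because the scale "assesses the severity of nocturnal and daytime components of insomnia over the past two weeks". The planned ANCOVA, imputation and mixed model need no change, since timely values already enter them.

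The cost is a short change to the approved wording and a few extra contacts. Anyone who has withdrawn consent to data collection is not contacted. Trial status reports that recruitment is complete and follow-up continuing, so the gain may be limited to remaining week-6 values. If none is still due, the by-arm report is what remains, and it helps readers judge the missing-at-random assumption.

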### Patient and public involvement

Patients or members of the public were not involved in the design, conduct, reporting or dissemination plans of this trial.

### Researchers training

Before participant enrolment, all investigators (acupuncturists, LLLT operators, assessors and data managers) will receive standardized training on the study protocol, operating procedures and data collection forms in order to ensure consistency across visits.

## Discussion

This protocol describes a randomized, assessor-blinded, superiority randomized controlled trial designed to compare wearable low-level laser therapy (LLLT) with manual acupuncture for the treatment of chronic insomnia. Acupuncture has accumulated evidence as an effective complementary therapy for insomnia (4–8), but its invasiveness, requirement for clinic-based treatment and dependence on practitioner skill may limit its accessibility and scalability. Wearable LLLT, applied to standardized acupoints, offers a non-invasive intervention with potential for future home-based implementation (9–12). By directly comparing these two active interventions that stimulate the same bilateral acupoints (HT7, PC6, and SP6), this trial aims to provide clinically meaningful evidence on whether LLLT produces greater improvement in insomnia severity than manual acupuncture.

Compared with previous trials, this study has several methodological strengths. First, it adopts a parallel-group randomized design with allocation concealment and blinded outcome assessment where feasible. This approach helps reduce selection bias and assessor-related bias for investigator-administered procedures such as HRV measurement, although it cannot eliminate expectation-related bias in patient-reported outcomes. Second, both groups receive rigorously standardized interventions, including clearly defined acupoint locations, treatment frequency and session duration, thereby enhancing reproducibility. Third, the trial incorporates both subjective and physiological outcome measures: the ISI and PSQI capture patients’ perceived insomnia severity and sleep quality, while HRV indices provide complementary information on autonomic regulation that may be associated with treatment-related changes. In addition, the use of validated questionnaires for fatigue, depressive and anxiety symptoms allows a broader evaluation of comorbid symptoms that are highly relevant in chronic insomnia.

The statistical analysis plan is also a strength of this protocol. The sample size is based on preliminary data and previous acupuncture trials, and the primary analysis follows a superiority framework using ANCOVA to adjust for baseline differences. The week-6 ISI follow-up will be examined using a supportive linear mixed-effects model, while secondary continuous outcomes assessed at week 2 will be analyzed using ANCOVA with adjustment for the corresponding baseline values. The use of both intention-to-treat and per-protocol analyses, together with prespecified missing-data handling, is expected to provide robust and transparent results.

Nevertheless, several limitations should be acknowledged. First, participants and treating practitioners cannot be blinded, and the primary endpoint together with most secondary endpoints is patient-reported. Accordingly, assessor blinding cannot fully protect the study from expectation effects, performance bias, or reporting bias. Second, the intervention period is relatively short (two weeks), although this schedule was informed by previous acupuncture studies and our pilot data. Longer treatment courses or repeated cycles might yield different or more sustained effects and should be evaluated in future studies. Third, the study is conducted at a single center within a traditional Chinese medicine hospital, which may limit the generalizability of the findings to other settings or healthcare systems. Fourth, the PSQI assesses sleep quality over the preceding month, which means that the week-2 PSQI analysis may not fully reflect within-treatment change over a 2-week intervention and should therefore be interpreted cautiously. Several device-characterization limitations should also be acknowledged. The temporal emission mode of the 650-nm output was not specified in the manufacturer’s documentation; therefore, whether the output is continuous-wave or pulsed remains unclear. In addition, no independent optical calibration, temporal waveform measurement, beam-profile assessment, or spatial power-distribution mapping was performed. As a result, the reported irradiance, fluence, and total energy values should be interpreted as protocol-level estimates based on manufacturer-reported specifications, the planned irradiation duration, and the observed visible illuminated area at the skin-contact surface, rather than directly measured optical parameters. This methodological limitation may restrict comparability with other photobiomodulation studies that report calibrated optical power, pulse structure, beam profile, and spatial power distribution. Nevertheless, because this is a protocol study, transparent reporting of the manufacturer-reported specifications, contact condition, estimated illuminated area, irradiation duration, and calculation assumptions provides a reproducible description of the planned intervention. Future studies should include independent optical calibration, temporal emission characterization, beam-profile assessment, and spatial power-distribution mapping to enable more precise dosimetric reporting. In addition, because six acupoints are irradiated simultaneously, potential cumulative or interaction effects across treated sites cannot be fully excluded and should be considered when interpreting clinical and physiological outcomes.

HRV is included in this trial as an exploratory physiological outcome reflecting autonomic regulation. However, in the present study HRV is derived from short-term resting PPG-based inter-beat interval recordings rather than from polysomnography, actigraphy, or full ECG-based sleep monitoring. Therefore, HRV should not be interpreted as a direct measure of sleep architecture or sleep continuity. We attempted to improve comparability by standardizing posture, room conditions, pre-test rest duration, recording duration, and pre-assessment behavioral restrictions. Nevertheless, peripheral perfusion, minor movement artifacts, time-of-day variation, and participant heterogeneity may still influence HRV estimates and should be considered when interpreting these findings. In addition, chronic insomnia is heterogeneous, and potential contributing factors such as hormonal, metabolic, or other medical drivers are not comprehensively characterized in this protocol, which may contribute to variability in treatment response.

In summary, this superiority randomized controlled trial will systematically evaluate the short-term effects of wearable LLLT compared with manual acupuncture in adults with chronic insomnia, with additional assessment of whether changes in insomnia severity are maintained at four-week follow-up. The findings are expected to inform clinicians and patients about the potential role of LLLT as a practical, non-invasive option within complementary and integrative sleep medicine. Regardless of whether the results demonstrate superiority or no meaningful difference between interventions, the trial will contribute valuable evidence to guide future research and clinical decision-making for chronic insomnia.

### Ethics and dissemination

The study protocol has been reviewed and approved by the Ethics Committee of Guangdong Provincial Hospital of Traditional Chinese Medicine (Approval No. YF2025-141-01). The trial will be conducted in accordance with the Declaration of Helsinki and relevant national regulations. Written informed consent will be obtained from all participants prior to enrolment. Participants may withdraw from the study at any time without prejudice to their routine care (34).

The results of this trial will be disseminated through publication in peer-reviewed journals and presentations at national and international conferences, regardless of whether the findings are positive, negative or inconclusive. De-identified data may be made available upon reasonable request after publication, subject to ethical approval and data-sharing agreements.

